### Criteria for discontinuing or modifying the allocated interventions

There will be no special criteria for modifying allocated interventions, but there are conditions under which to terminate the study: (1) unexpected postoperative continuation of intubation; (2) serious adverse events during the operation, such as acute massive hemorrhage, malignant fever, and shock; (3) unplanned reoperation within 24 h after surgery; (4) serious, adverse surgically related events/reactions occurring within 24 h after the operation, such as postcraniotomy hematoma, unconsciousness, coma, and cardiac arrest; and (5) serious adverse events/reactions related to the medicines in electronic analgesia pumps within 24 h after surgery.

### Strategies to improve the adherence to intervention protocols

The anesthesiologist who performs the SNB is well skilled and will be trained to perform the standard intervention method. The anesthesiologists in charge will be blinded when he/she performs anesthesia and records the intraoperative data. The investigator group will be blinded and well trained to perform preoperative recruitment and postoperative follow-up. Nurses in the PACU, ICU, or ward will be trained on how to use the electronic analgesia pumps and when to press the button of the electronic analgesia pump (nurse-controlled intravenous analgesia). In addition, participants and authorized surrogates will also explain the usage of electronic analgesia pump. Any deviations and missing data will be recorded.

### Blinding

After the patient’s enrollment, the independent anesthesiologist who performs the SNB will obtain the allocation randomized schedule from computer software operation. The allocation information of participants who are recruited and randomized will be placed in a sealed envelope and stored individually. Therefore, the anesthesiologist who performs the SNB will be the only person who knows the allocation schedule. This procedure ensures that both investigators and participants will not know the intervention.

Patients, anesthesiologists in charge of operation, and investigators who are responsible for enrolling and observing the primary and secondary outcomes will not know whether the children will receive blocking. The blinding will be discontinued after all data collection is completed. Furthermore, serious life-threatening adverse events leading to prolonged hospital stay or death will be reported to the principal investigator (PI), and the blinding will be broken following consultation with the PI if necessary.

### Data collection and management

Investigators will explain the benefits of participating in the trial to patients and their authorized surrogates before surgery. After the operation, a specific blinded investigator will conduct follow-up in the ward at 1, 2, 4, 24, and 48 h. Participants who are unable to complete the assessment of the primary outcome will be excluded in situations such as death or discharge in 24 h. Cases with other deviations and deficiencies except for the aforementioned conditions will be retained. Outcome investigators will receive training on all outcome measures. Nurses, children, and their authorized surrogates will be trained to use the electronic analgesia pump. All electronic analgesia pumps will be calibrated by a researcher according to uniform standards. The anesthesiologists in charge will record the patients’ intraoperative data. The relevant data of the electronic analgesia pumps will be recorded by an electronic memory system. The data are accessible to investigators who are blinded to the trial. A blinded investigator will collect other data on secondary outcomes, such as pain scores, postoperative complications, and length of hospitalization after surgery. The data managers will use double data entry to enter data into the EpiData database. An inspector will examine the data, create records, and revise these records as necessary.

Each participant will have a unique study identifier, and their data will be recorded by an independent data manager. The data will be electronically stored in the EpiData database and undisclosed to other researchers until the study is completed. The final dataset will be handed over to statistical analysts for statistical analysis. Regular data checks and double data entry will be applied to promote data quality.

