### Statistical analysis

Statistical analyses will be performed using SPSS 23.0 software. All measured data will be reported as the mean ± standard deviation ($$ \overline{x} $$ ± s), interquartile range (IQR, 25–75% percentile), or number (%). For normally distributed and equal-variance data, statistical analyses of categorical variables will be carried out using the *t* test or analysis of variance (ANOVA). For abnormally distributed and unequal variance data, statistical analyses of categorical variables will be carried out using a nonparametric test as appropriate. A chi-square test and Fisher’s exact test will be used to compare proportions. For the primary outcome, we will first use ANOVA to compare whether there are differences among the three groups. If there are differences, further multiple comparisons will be performed. The results of the FLACC scores, FACES scores, and NRS scores will be analyzed by repeated measurements for general linear models and multivariate analysis. We will also perform the subgroup analysis based on different ages. We will exclude patients who reject the intervention and whose primary data are missing. Statistical significance will be defined as a *P* value < 0.05.

All randomized participants with informed consent will be analyzed. If unintended missing data related to the primary outcome account for more than 10%, this will be handled with multiple imputation. Analyses will be performed according to the intention-to-treat principle.

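### Two exclusion rules remove randomized children from a primary analysis that the same article says will include everyone by intention to treat

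*Protocol article*

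**What the plan says.** Four statements in the protocol article bear on who enters the primary analysis.

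- **Data collection and management.** Participants "unable to complete the assessment of the primary outcome will be excluded in situations such as death or discharge in 24 h". The following sentence marks these off from everyone else: "Cases with other deviations and deficiencies except for the aforementioned conditions will be retained".
- **Statistical analysis, end of the first paragraph.** "We will exclude patients who reject the intervention and whose primary data are missing".
- **Statistical analysis, last paragraph.** "All randomized participants with informed consent will be analyzed", and "Analyses will be performed according to the intention-to-treat principle".
- **Same paragraph, on missing values.** "If unintended missing data related to the primary outcome account for more than 10%, this will be handled with multiple imputation".

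Three other places matter.

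- The Eligibility section lists inability to come off the ventilator after surgery as an exclusion criterion. The section on discontinuing the allocated intervention repeats it as a reason to terminate.
- That termination list also includes reoperation, serious surgical events and "serious adverse events/reactions related to the medicines in electronic analgesia pumps within 24 h after surgery".
- On the source of the primary value, the Data collection section says: "The relevant data of the electronic analgesia pumps will be recorded by an electronic memory system".

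**The concern.** The first two statements remove randomized children from the analysis, and the third says nobody with consent is removed. The article does not name a full analysis set and a per-protocol set to which the rules could separately belong.

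The exclusions arise after randomization. Allocation is made before the preoperative block, whereas death, early discharge and a missing 24-h total are known only after surgery. Such losses need not be independent of treatment or of pain. Death is both a listed safety outcome and a named reason for exclusion. A child whose pump is stopped after a drug reaction or a hematoma may end up without a usable 24-h total.

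At stake is the protection that randomization gives the primary comparison. An analyst handling a child with a partial total could exclude or include that child and cite the article either way.

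**Working it through.** **1. The rules side by side.** Each row is a consented, randomized child.

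| Child | Data collection section | Exclusion sentence in Statistical analysis | Closing paragraph of Statistical analysis |
|---|---|---|---|
| Dies or is discharged before 24 h | excluded | excluded, if the total counts as missing | analyzed |
| No 24-h total for another reason, missingness at or below 10% | unclear: the named situations are only examples | excluded | analyzed, but no rule supplies a value |
| Same, missingness above 10% | unclear | excluded | imputed |
| Refuses the block but has a 24-h total | retained | excluded or kept, depending on reading | analyzed |

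The first row is a direct contradiction. In the third row, a child excluded for a missing value cannot also be imputed.

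The exclusion sentence can describe two groups (refusers, and those with missing data) or one group meeting both conditions. If refusing means withdrawing consent and the one-group reading is meant, that sentence agrees with the closing paragraph. The first row still conflicts, because it also rests on the Data collection section.

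**2. The stated sample size and the 10% trigger.** Inputs from the Sample size section: 54 per group, 10% loss, three groups.

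- 54 / 0.90 = 60 per group and 3 × 60 = 180, as stated.
- Imputation starts above 0.10 × 180 = 18 children.
- Budgeted loss is 60 − 54 = 6 per group, or 18 in total.

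The largest number that can go unimputed therefore equals the loss already allowed for.

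**3. Size per child (illustration).** The article gives no SD or control mean, so the SD is back-solved. A two-sample t test with 54 per group, two-sided alpha 0.05/3 and 80% power detects d = 0.631. A 20% decrease then implies SD / control mean = 0.20 / 0.631 = 0.317; the normal approximation gives 0.321. Assume equal SDs across arms.

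Dropping one of 60 children who lies k SD from the arm mean moves that mean by k/59 SD:

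- k = 1: 0.0169 × 0.317 = 0.54% of the control mean.
- k = 2: 0.0339 × 0.317 = 1.07% of the control mean.

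At k = 2, a true 20% reduction would read:

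- child lost from a block arm: 20 ± 1.07, or 18.9 to 21.1%;
- child lost from the control arm, whose mean is also the denominator: 1 − 0.8/(1 ∓ 0.0107), or 19.1 to 20.9%.

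**4. Why a partial total is not a complete one.** Inputs from the Anesthesia and analgesia section: 2 μg/kg in 100 ml, 2-ml bolus, 30-min lock-out.

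- One bolus: 2/100 × 2 = 0.04 μg/kg.
- 24-h maximum: about 2 × 24 = 48 boluses, 48 × 0.04 = 1.92 μg/kg.
- Recording ends at 4 h: about 8 boluses at most, 0.32 μg/kg, which is 0.32/1.92 = 17% of the maximum.
- Discharge at 12 h: about 24 boluses at most are unobserved, 0.96 μg/kg.

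A truncated recording looks like low consumption whether it stopped because of death, a complication or discharge. Entering it as if complete would be wrong in all three cases. The pump settings also put a ceiling on any imputed amount.

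**The case against.** **The full protocol or analysis plan may settle this.** An article may leave detail out, but here it states two incompatible rules. A later document would have to overrule one of them.

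**The word unintended may separate imputable gaps from death or discharge.** Possibly, but that concerns imputation only. It does not reconcile excluding a randomized child with analyzing all of them.

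**The practical divergence is narrow.** This largely stands. At or below 10% missing, no rule supplies a value, so two analysts would probably both run ANOVA on the children who have a 24-h total. They would part over partial totals and over missingness above 10%. A reader might infer that the primary population is open in general; the article does not support that.

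**The events are few and already budgeted.** This also stands in part. The named cases are death or discharge within 24 h of elective tumor craniotomy, in children scheduled for follow-up to 48 h. The figure of 18 is a ceiling, not an expectation, and the sample size allows for it. With the back-solved SD, power is 80% with 54 per group and about 84.5% with 60. A reader might infer a loss of power; there is none beyond plan. The budget does nothing, however, about who is lost.

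**Terminated children.** A reader might infer that the termination list itself removes children from the analysis. It does not say so, and a terminated child may still have a full 24-h total in the pump memory. The exclusions apply only if that total is not obtained.

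**Deaths.** It is tempting to switch the primary test to ranks if any child dies. The article allows nonparametric tests for non-normal or unequal-variance data, not for deaths, and names ANOVA for the primary outcome. One death in 180 should not change the comparison on which the trial was sized.

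**Conclusion.** The conflict is real and should be fixed. As written, the exclusions and the promise to analyze all consented randomized children by intention to treat cannot both hold. At or below 10% missing, children without a 24-h total would be left out after randomization for reasons that may relate to outcome.

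A reader might go further and infer that the primary result will be biased, or biased toward a block arm. The documents do not support this: they give no event rate, and nothing indicates a direction. The effect is probably small, about 0.5 to 1.1% of the control mean per lost child. That range rests on a back-solved SD, equal SDs across arms and an assumed departure of 1 to 2 SD. The contradiction depends on none of these figures.

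**What to change.** **Data collection and management.** Replace the exclusion with a statement that all randomized children with consent are analyzed in their allocated group.

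**Eligibility, and criteria for discontinuing.** Reword the postoperative-intubation criterion in both places so that it ends study procedures but does not remove a randomized child from the analysis. Otherwise the new analysis set would contradict the eligibility list.

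**Statistical analysis.**

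- Delete the exclusion sentence.
- Use the full 24-h total from the pump memory wherever it was observed.
- Treat totals cut short by early discharge or an early pump stop as incomplete. Multiply impute them by group and age stratum at any level of missingness, not only above 10%. The bolus limit of 2 per hour (0.08 μg/kg) can cap the imputed part.
- Keep ANOVA as the primary test.
- Report deaths within 24 h by group and never count them as low consumption. Any value imputed for such a child in the ANOVA is hypothetical, so pre-specify a sensitivity analysis that addresses deaths directly, for example by worst rank.
- Report a complete-case analysis beside it.

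**Cost.** A short amendment to four sections and slightly more analysis work. No extra children are needed. Recruitment began in September 2018, so changes to follow-up can apply only to children not already terminated; for the others, use whatever pump-memory data were kept. The blind is to be lifted only after data collection is complete, so the rule can be fixed before anyone sees results by group.

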### Confidentiality

Before the trial, all personal information will be obtained only by the PI who has signed a confidential disclosure agreement. After randomization, during and after the trial, unique study identifiers will be assigned to each participant to reduce the risks of accidental disclosure of identifiable information. To protect confidentiality, paper information will be stored in a locked cabinet inside the locked research office. The electronic information will also be kept in a password-protected electronic database. The specific privilege assignments to access the database to acquire personal information will be limited by the role of the assignees in the trial. Only code numbers will appear on any data and documents used for evaluation or statistical analyses.

### Sample size

The primary outcome in this study is the total consumption of sufentanil within 24 h after surgery. A decrease of 20% will be considered a minimal clinically important difference. According to Maxwell’s article [30] and our experience, 54 subjects per group will be necessary with a two-sided *α* level of 0.017 (0.05/3) and 80% power. Considering a 10% rate of loss to follow-up, it would be necessary to include 60 participants per group (total: 180 participants). The sample size calculation is performed using PASS 15.0.

### Statistical analysis

Statistical analyses will be performed using SPSS 23.0 software. All measured data will be reported as the mean ± standard deviation ($$ \overline{x} $$ ± s), interquartile range (IQR, 25–75% percentile), or number (%). For normally distributed and equal-variance data, statistical analyses of categorical variables will be carried out using the *t* test or analysis of variance (ANOVA). For abnormally distributed and unequal variance data, statistical analyses of categorical variables will be carried out using a nonparametric test as appropriate. A chi-square test and Fisher’s exact test will be used to compare proportions. For the primary outcome, we will first use ANOVA to compare whether there are differences among the three groups. If there are differences, further multiple comparisons will be performed. The results of the FLACC scores, FACES scores, and NRS scores will be analyzed by repeated measurements for general linear models and multivariate analysis. We will also perform the subgroup analysis based on different ages. We will exclude patients who reject the intervention and whose primary data are missing. Statistical significance will be defined as a *P* value < 0.05.

All randomized participants with informed consent will be analyzed. If unintended missing data related to the primary outcome account for more than 10%, this will be handled with multiple imputation. Analyses will be performed according to the intention-to-treat principle.

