### Allocation and randomization

After meeting the eligibility criteria and signing the informed consent to participate in the study, 180 patients will be randomly allocated in a 1:1:1 ratio to three groups: group B (preoperative ropivacaine block group), group A (postoperative ropivacaine block group), and group N (nonblocking control group), stratified by age into two strata (aged 1–6 years and aged 7–12 years). The allocation schedule will be made with a computer random number list generated by Stata software version 15.1.

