### Outcomes measurement

Primary outcome: Total consumption of sufentanil within 24 h after surgery.

Secondary outcomes:
Assessment of postoperative pain scores at 1, 2, 4, 24, and 48 h after surgery: children aged 1–6 years: due to the special characteristics of children after neurosurgery and of preschoolers who cannot properly express their pain with language, two different scoring methods will be used—the FLACC scale and the FACES facial pain score. Children aged 7–12 years can use NRS for self-assessment in addition to the above two methods.Total consumption of sufentanil within 1, 2, 4, and 48 h after surgery and emergency-remedy medicine consumption at 1, 2, 4, 24, and 48 h after surgery.Postoperative safety indicators: complications including agitation, postoperative nausea and vomiting (PONV), bleeding, infection, hypoxemia, respiratory depression, neurological impairment at 1, 2, 4, 24, and 48 h after surgery, and serious adverse events including disability and death.Length of hospitalization after the surgery.

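### The plan does not say whether its general rule sending non-normal, unequal-variance data to rank tests overrides the ANOVA named for the primary outcome, and it names no unequal-variance comparison of means

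*Protocol article*

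**What the plan says.** All places are in the protocol article.

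- Outcomes measurement: "Primary outcome: Total consumption of sufentanil within 24 h after surgery".
- Sample size: "A decrease of 20% will be considered a minimal clinically important difference". The calculation uses a two-sided "level of 0.017 (0.05/3) and 80% power" and concludes that "54 subjects per group will be necessary", raised to 60 for 10% loss. It was done in PASS. No SD or control value is given, and the text does not say whether the decrease is in the mean.
- Statistical analysis, general rule: t test or ANOVA when data are normal with equal variance. Otherwise: "For abnormally distributed and unequal variance data, statistical analyses of categorical variables will be carried out using a nonparametric test as appropriate".
- Statistical analysis, primary outcome: ANOVA across the three groups first, then multiple comparisons if the groups differ. No condition is attached and the comparison method is not named.

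Both sentences of the general rule speak of categorical variables, although the tests they name are for continuous or ordinal data.

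**The concern.** The general rule makes ANOVA conditional on normality and equal variance. The same paragraph then prescribes ANOVA for the primary outcome and neither repeats nor waives the condition. Two analysts could follow this text in good faith and run different primary tests.

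If the general rule applies, what is tested depends on the observed data. The 20% decrease, the sizing in PASS and the choice of ANOVA all imply a difference in means. A rank test does not test a difference in means, gives no percentage reduction to set against 20%, and does not correct for unequal variance.

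The trigger is plausible here. According to Anesthesia and analgesia, the pump has no background infusion and delivers fixed-volume boluses on demand. Consumption is therefore a bolus count bounded at zero. Such data are often skewed, with a spread that rises with the mean, so a block that works could lower both the mean and the SD.

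If the general rule does not apply, ordinary ANOVA runs whatever the variances are. Pooled-error comparisons would then carry the wrong standard error for each contrast, including group A versus group B, which the Discussion gives as the second aim.

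**Working it through.** **1. The plan's own figure.** With the control mean scaled to 1 and a difference of 0.20, n = 2(z₁₋α/₂ + z₁₋β)² CV² / 0.20². For α = 0.05/3 and 80% power, (2.394 + 0.842)² ≈ 10.47. Setting n = 54 gives CV² = 54 × 0.04 / 20.94 ≈ 0.103, so CV ≈ 0.32. A CV of 0.32 returns n = 54, and 54/0.90 = 60. The figure of 54 cannot be derived forward because no SD is stated; the CV is back-solved.

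**2. If ANOVA governs and the comparisons use the pooled error.** Assume SDs of 1 (control), 0.8 and 0.8, that is, SD proportional to the mean under a 20% decrease. Use equal n and a normal approximation.

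- Pooled variance = (1 + 0.64 + 0.64)/3 = 0.76, so each contrast is given variance 2 × 0.76 = 1.52 (per n).
- Block versus control: true variance 1 + 0.64 = 1.64. Effective critical value 2.394 × √(1.52/1.64) = 2.305, two-sided rate ≈ 0.021.
- A versus B: true variance 0.64 + 0.64 = 1.28. Effective critical value 2.394 × √(1.52/1.28) = 2.609, two-sided rate ≈ 0.009.

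The nominal rate is 0.0167. The A versus B figure applies directly when both blocks work equally well, and it makes that comparison conservative. If SD is proportional to the mean, equal means imply equal SDs, so the 0.021 is best read as the non-coverage of the interval for the block-versus-control difference.

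**3. If the general rule governs: how often would a variance check fail?** Simulation, 54 per group, normal, gamma and lognormal data, constant CV, tests at 5%. The article names no variance test, so mean-centred Levene and Brown-Forsythe are assumed.

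- 20% decrease in both block groups: 25–34% at CV 0.32, and 19–35% at CV 0.6.
- No effect: Brown-Forsythe about 4–5%, mean-centred Levene 5–14%.

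Read literally, the rule also requires non-normality, so these rates cannot be taken as the rate of switching.

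**4. If a rank test is then used.** Mann-Whitney with equal means and unequal spread, pairwise level 0.017, 54 per group:

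| CV pair | Normal | Gamma | Lognormal |
|---|---|---|---|
| 0.322 v 0.258 (1.25:1) | 0.017 | 0.019 | 0.022 |
| 0.322 v 0.161 (2:1) | 0.020 | 0.037 | 0.052 |
| 0.6 v 0.3 (2:1) | 0.020 | 0.083 | 0.135 |
| 0.8 v 0.4 (2:1) | 0.021 | 0.145 | 0.200 |

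Welch's test stays at 0.016–0.023 throughout. With three groups, skewed data and CVs 0.6/0.3/0.3 at nominal 0.05, Kruskal-Wallis rejects 0.17–0.24 and ANOVA 0.060–0.066.

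**5. Power for the planned effect.** For a 20% decrease at constant CV 0.322: t test 0.87–0.88, Welch 0.87–0.88, Mann-Whitney 0.85–0.88. These exceed 80% because the SD in the block group is taken to fall with its mean.

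**The case against.** The strongest reply is that the sentence on the primary outcome is specific and unconditional, and a specific sentence normally prevails over a general one. A reader might infer that the plan states a switch for the primary outcome. It does not; it only leaves open whether the general rule reaches that far. This limits the point to an ambiguity but does not remove it, because ANOVA has just been made conditional and the primary outcome is not exempted.

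A reader might also infer that unequal variance alone sends data to a rank test. The rule joins non-normality and unequal variance with 'and' and adds discretion. Literally, data that fail only one condition are assigned to neither branch, which is a further gap.

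Third, a reader might carry the large rank-test error rates over to this trial. They require a block that roughly halves the spread without changing mean consumption, in skewed data. The article gives no reason to expect that. If SD follows the mean, equal means imply equal SDs and the rank test keeps its level; when spreads differ because the block works, rejection is a correct result. At the 1.25:1 ratio that matches the planned effect, inflation is negligible.

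Finally, a journal article may leave assumption checks and contrast methods to an analysis plan that is not shown. That is fair for the missing detail. It does not excuse a rule that the article does state and that offers a rank test as its only alternative to equal-variance methods.

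**Conclusion.** The point holds as a needed clarification with a modest numerical effect. The order of the two analysis sentences is unresolved, and either reading can be improved: one lets the data choose between means and ranks, and the other risks mildly miscalibrated pooled comparisons (about 0.021 and 0.009 against 0.0167). At the planned 20% decrease and a CV near 0.32, power differs little between methods, so what is at stake is mainly which hypothesis is tested and whether the result can be read against the 20% threshold.

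This rests on assumptions: the CV is back-solved, the distributions and the link between SD and mean are supposed, the variance test is not named in the article, and the 20% is taken as a decrease in the mean. It does not support a claim that the trial's type I error is seriously inflated.

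**What to change.** State that the primary outcome is analysed without a data-driven switch and that the general rule does not apply to it. Name either Welch ANOVA followed by the three unequal-variance pairwise contrasts (Games-Howell, or Welch tests at 0.05/3), or a linear model adjusted for age stratum with robust standard errors. Report each mean difference and percentage difference with its interval, so that it can be read against 20%. Keep a rank test as a labelled sensitivity analysis. Replace 'categorical' by 'continuous' in both sentences of the general rule.

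The cost is wording and standard software options. The sample size stays at 60 per group, since Welch matches the t test for power in the planned setting. The downside is somewhat less power than a rank test if the data prove strongly skewed.

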### Intervention

The corresponding SNB schemes of the three groups will be the following:
*Group B*: Preoperative SNB group (ropivacaine hydrochloride injection: Naropina®, AstraZeneca AB, Sweden): SNB will be performed after general anesthesia and endotracheal intubation.*Group A*: Postoperative SNB group: SNB will be performed after the end of the operation, and the effects of analgesics and sedatives will not wane.*Group N*: nonblocking control group: This control group will not undergo SNB.

SNB will be performed exclusively by a well-trained anesthesiologist with two age-appropriate concentrations of ropivacaine: 0.3% in children aged 1–6 years and 0.5% in children aged 7–12 years.

The site of SNB will be selected according to the craniotomy region. Dosage: supraorbital nerve (1–2 ml), auriculotemporal nerve (1–2 ml), zygomatic temporal nerve (1–2 ml), greater occipital nerve (2–3 ml), and lesser occipital nerve (2–3 ml). An experienced anesthesiologist will determine the injection points according to the surgical incision site. The total volume will not exceed 5 ml.

The independent anesthesiologist performing the SNB will not be an investigator in charge of the operation and will not visit patients before or after the operation. The anesthesiologist will enter the operating room twice, the first time is after endotracheal intubation prior to surgery, and the second time is after suturing the scalp. He/she will confidentially perform or not perform SNB according to the allocation plan and cover the dressing at the corresponding portion to conceal the allocation. Due to ethical care standards for children, normal saline will not be injected, and only a dressing will be covered in group N.

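### The primary ANOVA names no term for the age strata used in randomization; if age predicts sufentanil use, precision is lost on the conservative side

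*Protocol article*

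**What the plan says.** All references are to the protocol article.

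- **Allocation and randomization:** "180 patients will be randomly allocated in a 1:1:1 ratio to three groups", and this allocation is "stratified by age into two strata", 1–6 and 7–12 years.
- **Outcomes measurement:** "Primary outcome: Total consumption of sufentanil within 24 h after surgery". Neither this section nor Sample size says whether consumption is absolute (μg) or per kg.
- **Statistical analysis:** "For the primary outcome, we will first use ANOVA to compare whether there are differences among the three groups". Then: "If there are differences, further multiple comparisons will be performed". No stratum term or covariate is named for this outcome.
- **Statistical analysis, subgroups:** "We will also perform the subgroup analysis based on different ages". No interaction is mentioned, and the text does not say whether these subgroups are the two randomization strata.
- **Intervention:** the ropivacaine concentration follows the strata, "0.3% in children aged 1–6 years and 0.5% in children aged 7–12 years".
- **Anesthesia and analgesia:** a nurse controls the pump at ages 1–6. At 7–12 a nurse does so until the child can operate the button. The 100 ml bag holds 2 μg/kg sufentanil and each bolus is 2 ml.

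**The concern.** Stratified randomization balances the strata across groups. An analysis that omits the stratum leaves between-stratum variation in the error term, although the design has largely removed it from the group comparison. Standard errors are then too large, to the extent that stratum predicts the outcome.

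Two features make a link plausible. Button presses generate the primary outcome, and who presses differs by age. Also, each bolus is fixed per kg, so if consumption is analysed in absolute μg, heavier and older children receive more per press. The concentration difference is a weaker argument for a common stratum effect, because group N receives no block; it points instead to a treatment effect that may differ by stratum.

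At stake is precision in a trial sized at 80% power. For the subgroups, the stake is that two half-size strata, if tested separately, can easily disagree by chance.

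**Working it through.** **1. The plan's own figure.** Sample size gives 54 per group, two-sided alpha 0.017 (0.05/3), 80% power, a 20% decrease and 10% loss. The inflation reproduces: 54/(1 − 0.10) = 60 per group, 180 in total. The 54 cannot be derived forwards because no mean or SD is printed. Solving backwards with the normal approximation:

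d = (z₁₋₀.₀₀₈₅ + z₀.₈₀) × √(2/54) = (2.387 + 0.842) × 0.1925 = 0.621

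A 20% decrease with d = 0.621 implies an SD of 0.20/0.621 = 32% of the control mean. That is a possible input, so the 54 is not shown to be wrong.

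**2. Effect of adding the stratum.** Let R² be the share of outcome variance explained by age stratum. **It is assumed; the documents give none.** The residual SD becomes SD × √(1 − R²), so

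power = Φ( d√(54/2)/√(1 − R²) − 2.387 ), with d√27 = 3.228.

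The number per group for 80% power is 54(1 − R²), rounded up.

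| Assumed R² | Power with stratum in model | n per group for 80% |
|---|---|---|
| 0 | 80.0% | 54 |
| 0.05 | 82.3% | 52 |
| 0.10 | 84.5% | 49 |
| 0.20 | 88.9% | 44 |
| 0.30 | 92.9% | 38 |

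**3. What the unadjusted test does.** The 80% is the planned figure. If the groups are exactly balanced within strata, the estimate itself has variance reduced by (1 − R²) but is judged against the unreduced standard error. Unadjusted power is then Φ((3.228 − 2.387)/√(1 − R²)) = Φ(0.842/√(1 − R²)): 80.6%, 81.3%, 82.7% and 84.3% at R² of 0.05, 0.10, 0.20 and 0.30. With perfect balance the loss is therefore about 2, 3, 6 and 9 percentage points. Measured against the planned 80% it is 2, 5, 9 and 13 points. Both readings have the same sign.

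**4. Type I error of the three-group ANOVA at nominal 5%.** With 27 per group per stratum and exact balance, it is close to P(F > F₀.₉₅/(1 − R²)) on 2 and 159 degrees of freedom: 3.6%, 2.4% and 1.4% at R² of 0.10, 0.20 and 0.30. Simulation agrees (3.6%, 2.3%, 1.4% in 200,000 runs), and the stratum-adjusted test stays at about 5%. The error is conservative.

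**5. Subgroups.** No stratum sizes are given; equal strata are assumed, so 54/2 = 27 per group per stratum.

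- Pairwise power within one stratum at 0.05: Φ(0.621 × √(27/2) − 1.960) = Φ(0.323) = 63%.
- Chance that exactly one stratum is significant when the true effects are equal: 2 × 0.627 × 0.373 = 47%.
- Power of an interaction test at 0.05 when the two strata differ by the whole design effect: Φ(0.621/√(4/27) − 1.960) = Φ(−0.346) = 36%.

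**The case against.** The strongest reply is that this is missing detail, not a stated error. The article never says the ANOVA is one-way, an ANOVA with a stratum factor is still an ANOVA, and covariates are commonly left to an analysis plan that is not shown. This stands in part: a fuller document may already contain the term. But the article does fix the primary method, and as written it does not carry the stratification through.

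Second, the strength of the age link is not shown. The pump is to be pressed at one FLACC threshold with no age distinction, older children also start under nurse control, and analysing consumption per kg would largely remove the link through body weight. This stands, which is why every gain above is conditional on R².

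Four stronger readings are tempting, and the documents do not support them:

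- *The trial is biased or underpowered.* Omitting the stratum does not bias group means, and the planned power already refers to an analysis for which no adjustment is stated.
- *The subgroup results will mislead.* The single subgroup sentence does not say that strata will be tested separately or compared by their p-values. The 47% applies only if they are.
- *The day-0 pain score marked in Table 1 belongs in the primary model.* It is not a baseline of sufentanil use, nothing shows that it predicts that use, and the pain scales differ by age. Leaving it out is not an error.
- *The primary test may switch to a rank test.* The general rule on non-normal data is not clearly applied to the primary outcome, for which the text specifically names ANOVA.

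**Conclusion.** The point holds as a conditional loss of precision. The design stratifies by age and the stated primary analysis does not account for it. Under an assumed R² of 0.05 to 0.30, adjustment would give pairwise power of about 82% to 93% against the planned 80%; with exact balance within strata the gain over the unadjusted test is nearer 2 to 9 points. At R² = 0 nothing is lost. The figures rest on the effect size implied by 54 per group, the normal approximation and, for type I error and subgroups, equal and balanced strata.

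For the subgroups the conclusion is narrower: results could be misread if taken stratum by stratum. An interaction test is the proper frame but is weak here. It also cannot separate age from ropivacaine concentration or pump mode, because all three move together.

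**What to change.** 1. State the primary analysis as a linear model (ANOVA/ANCOVA) of 24-hour sufentanil on group and age stratum, with the three pairwise comparisons taken from that model.
2. State whether consumption is analysed in μg or μg/kg, since this affects how strongly age will predict it.
3. For the age subgroups, use the two randomization strata. Report the group-by-stratum interaction with stratum-specific estimates and 95% confidence intervals, labelled exploratory. Note that age is confounded with concentration and pump mode, and that the interaction test has low power.

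The cost is wording, plus one degree of freedom for the stratum term in the primary model. Age stratum is known for every randomized child, so no new data and no change to the sample size are needed. The change should be fixed before unblinding.
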